### Measurements

#### Demographic variables

At baseline, participants complete questions concerning demographic variables such as their marital status, living situation, religion, level of education, current job and working situation, and questions concerning the main earner in the family (relationship to the patient, annual income, occupation and source of income).

#### Trauma

The prevalence of trauma in childhood is measured by means of a Dutch translation of the short form of the Childhood Trauma Questionnaire (CTQ) [44]. The CTQ is administered only at the start of treatment (T1). The CTQ is a retrospective, self-report questionnaire that measures five categories of childhood trauma experience, including emotional, physical and sexual abuse as well as emotional and physical neglect. Each subscale is measured in 5 items rated on a 5-point Likert scale: (1) never true, (2) rarely true, (3) sometimes true, (4) often true, and (5) very often true. Each subscale score ranges from 5 (no history of abuse or neglect) to 25 (very extreme history of abuse and neglect). Cutoff scores are defined for none (or minimal) to low, low to moderate, moderate to severe and severe to extreme exposure. Moderate to severe cutoff scores were used to classify subjects as positive for a history of childhood trauma in a specific category. Cutoff scores are 13 or higher for emotional abuse, 10 or higher for physical abuse, 8 or higher for sexual abuse, 15 or higher for emotional neglect, and 10 or higher for physical neglect. Research has shown good psychometric properties for both the original CTQ version [44,45] and the Dutch translation [46].

#### Primary outcome measure

##### Symptom severity

General psychopathological symptoms are assessed with the Dutch version of the Brief Symptom Inventory (BSI) [37,38]. The BSI is the short version of the Symptom Checklist-90. It consists of 53 items covering nine symptom dimensions (somatization, obsession-compulsion, interpersonal sensitivity, depression, anxiety, hostility, phobic anxiety, paranoid ideation and psychoticism) and yields three global indices of distress: Positive Symptom Distress Index, Positive Symptom Total, and Global Severity Index (GSI). Possible GSI scores range from 0 to 4, with higher scores indicating a higher level of psychological and emotional distress. Respondents have to rate each item (e.g., “your feelings are easily hurt”) on a five-point scale ranging from 0 (not at all) to 4 (extremely), representing the intensity of distress relating to each item during the past 7 days. The reliability of the Dutch version of the BSI is good (Cronbach’s α ranging from .71 to .88, test-retest reliability ranging from r = .71 to .89). These values are comparable to the original BSI version of Derogatis [38].

#### Secondary outcome measures

##### Parasuicidal behaviour

Suicide and self-harm are assessed with the Suicide and Self-Harm Inventory (SSHI) [3]. The SSHI is a semi-structured interview assessing (a) the frequency and severity of suicidal acts in the past 6 months, and (b) the frequency and severity of acts of self-mutilation in the past 6 months. Multiple acts of self-mutilation over a short period of time – for example, frenzied self-cutting – are counted as a single act.

##### Symptomatic distress

Symptomatic distress is assessed with the Beck Depression Inventory (BDI-I), and the Measurements in the Addictions for Triage and Evaluation (MATE).

The BDI-I is used to assess depressive symptoms [47,48]. The BDI-I is a self-report instrument that consists of 21 questions concerning depressive symptoms during the past week. Each question has a set of four possible answers, ranging in intensity from 0 to 3, for example, “I don’t feel sad” (0) to “I feel so sad or unhappy that I cannot bear it anymore” (3). The total scores for the instrument are categorized: 0–9 no depression, 10–18 mild-moderate depression, 19–29 moderate-severe depression, 30–63 severe depression. The BDI has shown good psychometric qualities for both the original [47,48] and the Dutch version [49-51].

The substance use section of MATE 2.0 [52] is used to assess substance abuse and dependency. This section, which is designed as an interview, asks about the use of psychoactive substances in the past month and during the lifetime. The interviewer in this study was an MSc-level psychologist. The interrater reliability of this instrument ranges between 0.75 and 0.92 [53].

##### Attachment and mentalizing capacities

Attachment is assessed with the Experiences in Close Relationships (ECR) questionnaire. Mentalizing capacities are measured by the Reflective Functioning Questionnaire (RFQ), the Reading the Mind in the Eyes Test (RMET), and the FaceMorph task.

A Dutch translation of the Experiences in Close Relationships questionnaire (ECR) [54,55] measures adult attachment in romantic relationships. It contains two subscales: Anxiety (sample item: “I worry about being abandoned”) and Avoidance (“I feel very uncomfortable when my partner wants to have a close connection to me”) both consisting of 18 items. Individuals are asked to rate each statement on a 7-point Likert scale ranging from 1 (disagree strongly) to 7 (agree strongly). The Dutch version of the ECR was found to be a valid measure with good internal and external validity [55].

The RFQ assesses reflective functioning (a close proxy for mentalizing capacities) with 57 items that are rated on a 7-point scale (1 = strongly disagree to 7 = strongly agree). An example item is “People's thoughts are a mystery to me." As this measure is still under development, no psychometric data are yet available.

The Reading the Mind in the Eyes Test (RMET) [56] was developed as a measure of capacities in adults. Patients are shown photographs of 36 pairs of eyes, and have to match the eyes in each picture with one of four written expressions describing different emotions. In this study, a Dutch version of the RMET is being used [57].

The FaceMorph task is an experimental computerized task assessing capacities based on external features (i.e., facial expressions) of others. Morphed faces representing five emotions (happiness, sadness, anger, surprise, and fear) are shown on a screen at six different intensities (20%, 30%, 40%, 50%, 60%, and 70%) in random order. Every emotion is shown three times for each level of intensity, resulting in a total of 90 trials. Patients are asked to name the emotion they see and indicate their level of confidence in their choice on a 6-point Likert-type scale. Morphed facial emotion expressions are based on the NimStim dataset [58]. The dependent measures are accuracy, level of confidence in correct and wrong responses, and reaction time.

##### Personality pathology

Personality functioning is assessed with the Severity Indices of Personality Problems (SIPP-118) and the Personality Assessment Inventory-Borderline (PAI-BOR).

The SIPP-118 [59] is a dimensional self-report measure assessing the severity of personality pathology. The SIPP aims to assess the core components of adaptive and maladaptive personality functioning. It consists of 118 items, and comprises 16 facets that cluster into five higher-order domains: social concordance, relational functioning, self-control, responsibility, and identity integration. The SIPP-118 asks respondents to think about the past 3 months and to answer with the extent to which they agree with statements such as “I frequently say things I regret later” or “Whenever I feel something, I can almost always name that feeling”. Items are rated on a 4-point Likert-type scale ranging from 1 (fully disagree) to 4 (fully agree). Higher scores for each facet indicate better functioning. The psychometric features of the SIPP-118 are good, with evidence for good reliability (alpha coefficients ranging from .62 to .89, with a mean estimated α score of .78), convergent validity [59], and invariance of the factor structure [59].

The Dutch version of the PAI-BOR [60,61] was used to assess borderline symptomatology. The PAI-BOR is part of the Personality Assessment Inventory [60] and consists of four subscales (each with six items), which reflect four characteristics of BPD: affective instability (AI), identity problems (IP), negative relationships (NR), and self-harm (SH). There are four response categories (0 = false, 1 = slightly true, 2 = mainly true, and 3 = very true). An example item is “Sometimes I feel very empty inside”. A total PAI-BOR raw score of 38 or more indicates the presence of significant BPD features, whereas a score of 60 or more indicates typical borderline personality functioning [60]. The internal consistency (Cronbach’s α) and 6-month test-retest correlation for both the sum score and the sub domains are good.

##### Quality of life

Quality of life is measured using the EuroQol EQ-5D-3 L [62]. This self-report questionnaire provides a simple method to capture health problems according to a five-dimensional classification: mobility, self-care, usual activities, pain/discomfort, and anxiety/depression. Each dimension is divided into three levels: no problem, moderate problems, and extreme problems. The five dimensions can be summarized into a “value”, based on the preferences of the general public. These values can be used as societal weights for the calculation of Quality Adjusted Life Years (QALYs) in health economic evaluations (see also below). To calculate these societal weights, we used a Dutch validation study [63]. Adjacent to the five dimensions, the EuroQol presents a vertical visual analogue scale, ranging from 0 (worst imaginable health) to 100 (best imaginable health), on which the respondent marks the point that they feel represents their current health. The values on this scale are seen as representing patients’ values, in contrary to the societal weight based on the five dimensions. The reliability of the EQ-5D-3 L has been investigated and found to be acceptable [64], and it has shown to be sensitive to change in patients with personality disorders [14,65].

##### Social and interpersonal functioning

A Dutch translation of the Inventory of Interpersonal Problems (IIP-64) is used to assess interpersonal problems [66,67]. The IIP-64 is a self-report measure consisting of 64 items, assessing eight dimensions of interpersonal problems: (1) domineering/controlling (sample item: “It is hard for me to take instructions from people who have authority over me”), (2) vindictive/self-centred (“It is hard for me to trust other people”), (3) cold/distant (“It is hard for me to show affection to others”), (4) socially inhibited (“It is hard for me to introduce myself to someone”), (5) non-assertive (“It is hard for me to be firm when I need to be”), (6) overly accommodating (“It is hard for me to be angry at others”), (7) self-sacrificing (“It is hard for me to be angry at someone I like”), and (8) intrusive/needy (“It is hard for me to be on my own”). Respondents are asked to consider each problem and to rate how distressing that problem has been on a scale ranging from 0 (not at all) to 4 (extremely). The IIP-64 has shown good psychometric properties for both the original and the Dutch version [66,67].

##### DSM-IV Axis I and Axis II diagnoses

The Dutch version of the SCID-I [41,68] is used to assess Axis I disorders at intake and again at 36-month follow-up. The interviewer is an MSc-level psychologist, who was trained by an expert trainer in the SCID-I and SCID-II. The SCID-I has good interrater reliability (K = .85), especially when interviewers receive training as in the present study [69]. The Dutch version of the SCID-II [39,70] is used for diagnosing Axis II personality disorders at intake and at 36-month follow-up. No interrater reliability data will be collected in this study. Previous research has shown that both the original SCID-II and the Dutch version have good interrater reliability and test–retest interrater reliability in adults [71-73].

##### Costs

The intervention costs of MBT-DH and MBT-IOP will be calculated using a mixture of top-down and bottom-up approaches. The intervention costs estimates will include personnel costs, implementation costs (e.g., hosting and coaching), and any other overhead costs associated with the treatment. Medical costs beyond the intervention costs specific to MBT-DH and MBT-IOP will be calculated using the Trimbos and Institute for Medical Technology Assessment Questionnaire on Costs Associated with Psychiatric Illness (TiC-P) [74-76]). The TiC-P will be used to measure health care utilization at baseline and after 6, 12, 18, 24, and 36 months.

The first part of the TiC-P consists of questions on (1) the number of visits to, for example, a general practitioner, psychiatrist (outside MBT-DH or MBT-IOP), medical specialist, physiotherapist or alternative health practitioner; (2) the day care/hospital lengths of stay (outside MBT-DH or MBT-IOP); and (3) the use of medication in the 4 weeks prior to filling out the questionnaire [74]. These values are multiplied by the unit prices of the corresponding health care services according to the Dutch manual for costing studies in health care [76,77]. The unit prices will be adjusted to 2014 prices using the Consumer Price Index [78]. As the mean direct costs are measured per 4 weeks, we will multiply these values by 13 to obtain estimates for the annual costs.

The Tic-P also asks the patient to report any productivity losses, that is, absence from work or reduced productivity at work. This is used to estimate the so-called “friction costs”, that is, the monetary representation of the replacement of the labour. The friction-cost method takes the employer's perspective and counts as “lost” only those hours not worked until another employee takes over the patient's work. This is a more conservative estimate than the so-called “human capital method”, which relates productivity costs to the labour costs of the patient on a one-to-one basis. The choice between friction costs and human capital is still a subject of debate among economists. In this study, we chose the more conservative friction-cost method [79,80].

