**Methods/Design:**

A multicentre randomized controlled trial comparing MBT-DH versus MBT-IOP in severe BPD patients. Patients are screened for BPD using the Structured Clinical Interview for DSM-IV Axis II Personality Disorders, and are assessed before randomization, at the start of treatment and 6, 12, 18, 24, 30 and 36 months after the start of treatment. Patients who refuse to participate will be offered care as usual in the same treatment centre. The primary outcome measure is symptom severity as measured by the Brief Symptom Inventory. Secondary outcome measures include parasuicidal behaviour, depression, substance use, social, interpersonal, and personality functioning, attachment, mentalizing capacities, and quality of life. All analyses will be conducted based on the intention-to-treat principle. Cost-effectiveness will be calculated based on costs per quality-adjusted life-year.

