### Procedure

All patients referred to one of the mental health care centres are invited for a standard intake interview, which includes standardized assessment by means of the Structured Clinical Interview for DSM-IV Axis I disorders (SCID-I) [41] and SCID-II [39]. All patients eligible for MBT treatment (with a BPD diagnosis and aged ≥18 years) are given both written and verbal information about the study. Eligible patients are given 1 week to consider participation in the trial. Patients who are willing to participate in the study are asked to sign an informed consent sheet and complete the baseline assessment. Next, they are randomized to either MBT-DH or MBT-IOP by an independent researcher using a computerized 1:1 algorithm. Patients are informed about their treatment allocation and placed on a waiting list. One week prior to start of the main treatment phase, and subsequently at 6-months intervals up to 36 months after the start of treatment, patients complete an assessment battery as described below. Patients who are excluded from the trial on the basis of exclusion criteria, or who refuse to participate in the trial, are ideally assigned to an alternative evidence-based treatment. Excluded and refusing patients are asked to complete the baseline assessment only, for which they sign a separate informed consent form. At 18 and 36 months, the SCID-I and SCID-II are re-administered by MSc-level psychologists. Extensive efforts are being made to collect data at the follow-up time points by means of an outreaching approach towards patients: patients are contacted by telephone, e-mail and letters (with reminders as necessary) to motivate them to attend assessments, and home visits are made if necessary.

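### The cost questionnaire skips the 30-month visit, leaving one 4-week cost window in year 3, and the protocol gives two different SCID schedules

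*Protocol article*

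**What the plan says.** **Cost questionnaire.** The Costs section of the protocol article gives a closed list of times: "The TiC-P will be used to measure health care utilization at baseline and after 6, 12, 18, 24, and 36 months". The general schedule is denser. The abstract (Methods/Design) lists assessments at "6, 12, 18, 24, 30 and 36 months after the start of treatment", the Design section also has them every 6 months, and the Procedure section says that "at 6-months intervals up to 36 months after the start of treatment, patients complete an assessment battery as described below". The sample size section counts seven repeated measures, which matches start of treatment plus six half-yearly visits.

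**Recall and scaling.** Medication, for example, is recorded as "the use of medication in the 4 weeks prior to filling out the questionnaire", and the section continues: "As the mean direct costs are measured per 4 weeks, we will multiply these values by 13 to obtain estimates for the annual costs". The costs of MBT-DH and MBT-IOP themselves are calculated separately from the TiC-P.

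**Use of the data.** The Health economic evaluation section bases the primary cost-effectiveness ratio on observed trial data over a 3-year horizon.

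**SCID.** The Procedure section states: "At 18 and 36 months, the SCID-I and SCID-II are re-administered by MSc-level psychologists". The section on DSM-IV Axis I and Axis II diagnoses, placed under the secondary outcome measures, says that the SCID-I "is used to assess Axis I disorders at intake and again at 36-month follow-up", and gives the same two occasions for the SCID-II.

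**The concern.** The 30-month visit exists, but the instrument that supplies all costs outside the programmes is not listed there, and no reason is given. It may be a deliberate reduction of burden or a slip in the list; the article does not say.

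The gap falls at a sensitive time. The Background section puts both programmes at 18 months, so in year 3 the costs should be mostly those that the TiC-P records. The protocol's own evidence shows that late costs can diverge. In the earlier day-hospital trial, costs at 18-month follow-up were $3,183 against $15,490 under usual treatment. That is a different comparison from the present one, but it shows where an offset might appear. Cost-effectiveness is a stated aim, and the incremental cost is the numerator of its main ratio.

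The SCID conflict is a separate matter with no bearing on costs. It determines whether diagnostic status at 18 months, about the end of the programmes, will be available.

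**Working it through.** **1. The plan's own factor.** 52 weeks / 4 weeks = 13. The annualisation is correct.

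**2. Where the recall windows fall.** Month m is week m × 52/12, and the window is the 4 weeks before it. The post-baseline windows are weeks 22–26, 48–52, 74–78, 100–104 and 152–156. Year 3 runs from week 104 to week 156 and contains one window, the last. The month-24 window closes year 2 and can serve only as the left end of an interpolation. Observed time after baseline is 5 × 4 = 20 of 156 weeks (13%); with month 30 it would be 24 of 156 (15%).

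**3. Weights.** Assume annualised rates joined by straight lines (trapezoid), with the baseline value taken as month 0. Weights in years are:
- stated schedule (0, 6, 12, 18, 24, 36): 0.25, 0.5, 0.5, 0.5, 0.75, 0.5; sum 3.0
- with month 30: 0.25, 0.5, 0.5, 0.5, 0.5, 0.5, 0.25; sum 3.0
- year 3 alone, stated: 0.5, 0.5; with month 30: 0.25, 0.5, 0.25; each sums to 1

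**4. Precision.** Assume equal variance of every window and a common within-patient correlation r. The variance is then proportional to (1 − r) × Σw² + r × (Σw)².
- Σw² over three years: 1.625 stated, 1.375 with month 30. Year 3: 0.50 and 0.375.
- r = 0, year 3: √(0.50/0.375) = 1.155, so +15%. Three years: √(1.625/1.375) = 1.087, so +9%.
- r = 0.5, year 3: (0.5 × 0.50 + 0.5 × 1) = 0.75 against (0.5 × 0.375 + 0.5 × 1) = 0.6875; √(0.75/0.6875) = 1.044, so +4%. Three years: (0.5 × 1.625 + 0.5 × 9) = 5.3125 against (0.5 × 1.375 + 0.5 × 9) = 5.1875; √(5.3125/5.1875) = 1.012, so +1%.

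**5. Possible error in the year-3 estimate.** Let M be the mean of the month-24 and month-36 rates and k × M the month-30 rate (k is an assumption). Without month 30 the year-3 cost is M. With it, the cost is 0.5M + 0.5kM = M(1 + k)/2. The relative error is 2/(1 + k) − 1:

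| k | 0.5 | 0.75 | 1 | 1.5 | 2 |
|---|---|---|---|---|---|
| error | +33% | +14% | 0% | −20% | −33% |

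**6. SCID.** Procedure: repeat at 18 and 36 months, both instruments. DSM-IV diagnoses section: intake and 36 months, both instruments. Month 18 is in one and not in the other, so both cannot describe the schedule.

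**The case against.** Instruments need not all follow the general schedule. The childhood trauma questionnaire, for instance, is given only at the start of treatment, so a shorter TiC-P list may be intended. Costs and utilities may also be integrated on different time grids without error. Both points stand: the omission is not shown to be a mistake. It is nevertheless unexplained, and it conflicts with a Procedure section that has the battery completed at every half-yearly visit.

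The loss of precision may be small. Repeated costs in one patient are probably positively correlated, and at r = 0.5 the three-year loss is only about 1%. The TiC-P is also only one part of total cost. This stands too, and the independent-window figures should be read as the upper end among the two cases shown.

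A reader might infer more from the scaling rule: that 13 is the wrong multiplier for half-yearly visits, that 6.5 should replace it, and that cost could be overstated by 67% because five annualised values amount to five years in a 3-year horizon (5/3 = 1.67). The document does not support this. The factor is offered only to obtain an annual figure; an annual rate held for half a year is 13 × 0.5 = 6.5 times the 4-week cost, so the two rules agree. Nowhere does the article say that annual values are summed over visits. How they are combined is detail that an article may leave to the full protocol or analysis plan.

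A reader might also count two windows for year 3. The month-24 window belongs to year 2.

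**Conclusion.** Two schedule conflicts stand.

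First, the TiC-P list omits a visit that three other parts of the protocol schedule, so year-3 costs outside the programmes rest on one 4-week window plus interpolation from month 24. The loss of precision is modest and lies between the figures for r = 0 and r = 0.5 if the correlation lies in that range. The possible error in the year-3 level is larger, but it depends wholly on how far the month-30 cost rate departs from a straight line; it is zero if there is no departure. Whether it biases the comparison depends on whether that departure differs between arms, which cannot be known from the document. All these figures concern the TiC-P component only.

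Second, the SCID schedule contradicts itself on month 18. This is a wording error with a practical consequence for data collection. Diagnostic status is not among the secondary outcomes listed in the abstract or the research aims, so the point adds no weight to the costing one.

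The scaling by 13 is sound.

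**What to change.** Add the TiC-P to the existing 30-month visit and insert month 30 in the list in the Costs section. The cost is one more questionnaire at a visit that already takes place. Recruitment began in January 2012 and follow-up counts from the start of treatment, so the earliest 30-month visit could not fall before July 2014. If the omission is intended, or some of these visits have already passed without the TiC-P, the Costs section should say so and give the reason.

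Reconcile the Procedure section with the section on DSM-IV diagnoses, so that both state the same occasions for the SCID-I and SCID-II and it is settled whether 18-month diagnostic status is collected. This costs only a change of wording.

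The multiplier of 13 needs no change.
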